#### Statistical Analysis

Shapiro–Wilk test will be used to determine normality. For parametric distributions, dependent or independent *t* tests will be performed. To determine differences between categorical variables, the chi-squared test will be used. For nonparametric distributions, we will use the Wilcoxon test and Mann–Whitney *U* test to compare nonrelated and related means, respectively. A generalized estimating equations (GEE) model will be used to investigate multivariate repeated measurements. The Hayes method will be used to analyze the mediators (52), and the multivariate regression will be used to analyze the confounders. *Post hoc* analyses will be performed using the Bonferroni test.

The data will be expressed as mean ± standard deviation (SD), and a *p* value less than or equal to 0.05 will be considered to be statistically significant (two-tailed). The statistical analyses will be performed using the SPSS version 20.0 software package (IBM^®^, New York, USA).

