**Methods:**
*Design:* longitudinal, naturalistic. *Participants:* One hundred twenty-six patients who underwent one of three evidence-based modalities of individual psychotherapy [psychodynamic psychotherapy (PDT), interpersonal psychotherapy (IPT), and cognitive–behavioral psychotherapy (CBT)] were included. *Measure:* Primary outcomes are divided into three domains of variables: clinical (general psychiatric symptoms), biological (serum BDNF levels), and psychosocial (resilience, quality of life, coping strategies, social support, and quality of life-adjusted years of life). Confounding/mediator variables included clinical (personality traits, type of psychotherapy, number of sessions, concomitant use of pharmacological treatment, history of previous psychotherapeutic treatment, medical and psychiatric comorbidities, and psychiatric diagnosis), psychosocial (psychosocial stressors, therapeutic alliance, and defense mechanism style), and other (religiosity) factors. *Procedure:* The follow-up period will be baseline and 6 months and 1 year after entering the study. The study will include 42 controls for biological variables only. Sample size calculation considered a significance level of 5% and a power of 80% to detect a difference of 0.22 with a standard deviation of 0.43, assuming losses of 20–30% of patients. The comparison between the modalities of psychotherapy will be by generalized estimating equations (GEE) model, the analysis of mediators by the Hayes method, and confounders by multivariate logistic regression.

**Discussion:** The findings of this study are intended to demonstrate the outcomes of evidence-based psychotherapies for clinical, psychosocial, and biological parameters and to understand the mediators and confounders of this process in a real-life setting for patients with severe mental illness, thus contributing to the establishment of evidence-based public health policies in the field of psychological interventions.

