## Aims

Our primary aim is to evaluate the outcomes associated with different forms of individual psychotherapy [psychodynamic psychotherapy (PDT), interpersonal psychotherapy (IPT), and CBT] in a public outpatient clinic for mental disorders. Our primary outcomes are divided into three domains of variables: clinical (general psychiatric symptoms), biological (serum BDNF levels), and psychosocial (resilience, quality of life, social support, and quality of life-adjusted years of life).

Our secondary aim is to evaluate potential confounders/mediators/moderators for the main outcomes: personality traits, type of psychotherapy, number of sessions, the therapist’s duration of training, concomitant use of pharmacological treatment, history of previous psychotherapeutic treatment, medical and psychiatric comorbidities, psychiatric diagnosis, therapeutic alliance, and defense mechanisms.

Our main hypothesis is that all three modalities of therapy will produce reduction of symptoms in the clinical domain and improvement in the psychosocial domain. All psychotherapies will increase BDNF at 6 months of follow-up. As secondary hypotheses, the mechanisms of improvement will be mediated by the therapeutic alliance, motivational status, and defense mechanisms (for PDT). The confounders of this therapeutic improvement will be number of sessions, comorbidities, and medication use. The moderating factors will be gender, age, personality traits, religiosity, and defense mechanisms (for CBT).

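### The two rank tests for non-normal data are named the wrong way round, so before-after comparisons that fail the normality check would go to an unpaired test; as a lesser point, the abstract and the analysis section name different regressions for confounders

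*Protocol article*

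**What the plan says.** The Statistical Analysis section of the protocol article first tests normality with Shapiro–Wilk and then splits the two-sample comparisons by the result.

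- Normal data: "For parametric distributions, dependent or independent *t* tests will be performed".
- Non-normal data: "we will use the Wilcoxon test and Mann–Whitney *U* test to compare nonrelated and related means, respectively".
- Longitudinal data: "A generalized estimating equations (GEE) model will be used to investigate multivariate repeated measurements". The abstract adds: "The comparison between the modalities of psychotherapy will be by generalized estimating equations (GEE) model".
- Confounders, in the Statistical Analysis section: "the multivariate regression will be used to analyze the confounders".
- Confounders, in the abstract's Methods paragraph: "confounders by multivariate logistic regression".

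The Aims section lists the primary outcomes as "clinical (general psychiatric symptoms), biological (serum BDNF levels), and psychosocial (resilience, quality of life, social support, and quality of life-adjusted years of life". Table 1 gives the measures: BDI, BAI, SCL-90-R, serum BDNF, WHOQOL-BREF, CD-RISC, MOS and SF-6D. All are scale scores or a serum level. The article defines no cut-off or responder rule for any of them as an outcome.

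**The concern.** The order of the names in the rank-test sentence fixes which test goes with which design. Mann–Whitney U treats its two samples as independent. Applied to the same patients before and after therapy, it ignores the pairing and uses the wrong variance. The paired rank test is the Wilcoxon signed-rank test.

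This matters because the main hypothesis in the Aims section is about change within patients: symptoms fall, psychosocial scores improve and BDNF rises at 6 months. The Sample Size Estimation section also builds on BDNF before and after psychotherapy. An analyst who follows the text literally would, for any outcome that fails Shapiro–Wilk, run an unpaired test on the kind of comparison the study was sized for.

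The confounder wording is a smaller matter. Logistic regression needs a binary outcome and none is defined, so the abstract's method cannot be run on these outcomes as described. The analysis section does not repeat the word logistic, so the two places disagree. Confounder control is important here because modality is chosen by clinical judgment, using personality disorder and number of diagnoses among other features (Participants section).

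**Working it through.** **Step 1. Which comparison does the sample size rest on?** Inputs from Sample Size Estimation: difference 0.22, SD 0.43, significance 5%, power 80%, losses 20–30%, 42 per group. The two-sided test is from Statistical Analysis.

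Paired, normal approximation: n = ((1.960 + 0.842) × 0.43 / 0.22)² = 29.98, so 30. Paired t test: 31.96, so 32.

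Allowing for losses:

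- 30 / (1 − 0.25) = 40
- 30 / (1 − 0.30) = 42.9, so 43
- 32 / (1 − 0.25) = 42.7, so 43
- 32 × 1.30 = 41.6, so 42

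The stated 42 is therefore reproduced by a paired calculation. Two independent groups would need 2 × 29.98 = 59.97, so 60 per group before losses, and 75 (60 / 0.80) to 86 (60 / 0.70) after. That does not give 42. The planning comparison is before-after.

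**Step 2. Can the sentence be read so that it is right?** If Wilcoxon means the rank-sum test, the first half is correct, since that test is equivalent to Mann–Whitney and suits unrelated samples. The second half still assigns Mann–Whitney U to related samples, and no reading makes that a paired test. If Wilcoxon means the signed-rank test, both halves are wrong.

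**Step 3. What would literal use cost?** With per-visit variance σ² and before-after correlation ρ, the mean change has variance 2σ²(1 − ρ)/n. An unpaired test in effect presumes 2σ²/n. For ρ > 0 the presumed variance is too large, so the test rejects too rarely.

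Simulation settings: 32 pairs, bivariate normal data, true change 0.22 or 0, change SD held at 0.43 (per-visit SD = 0.43 / √(2(1 − ρ))), two-sided 5%, 5,000 runs per setting. The article gives no correlation, so the values of ρ are assumptions.

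| Assumed ρ | Power, Mann–Whitney | Power, signed-rank | Type I error, Mann–Whitney | Type I error, signed-rank |
|---|---|---|---|---|
| 0 | 79.2% | 78.5% | 4.7% | 4.8% |
| 0.3 | 65.5% | 78.2% | 1.9% | 4.6% |
| 0.5 | 49.6% | 77.5% | 0.8% | 4.7% |
| 0.7 | 23.4% | 78.3% | 0.1% | 5.0% |

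There is no loss at zero correlation and a large one at 0.7.

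**Step 4. The confounder wording, side by side.** The abstract says logistic. The Statistical Analysis section names a regression without a type. Table 1 contains only scores and a serum level as primary outcomes. The two statements agree only if the unspecified regression is logistic, and that would need a binary outcome the article does not define.

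**Step 5. Can every confounder be a baseline covariate?** The section on confusion, mediator and moderator factors lists diagnosis, medication use, number of sessions and comorbidities as confounders. Table 1 records diagnosis and comorbidities at baseline only, medication at all three visits, and number of sessions only at 6 and 12 months. Number of sessions has no baseline value, so a rule of baseline covariates only could not be carried out.

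**The case against.** The strongest reply is that two test names have been transposed. The sentence just before, on t tests, distinguishes dependent from independent samples, so the authors evidently intend paired tests for paired data. The error sits only in the fallback for non-normal data, and the longitudinal model is a GEE. All of this stands. It limits the reach of the error but does not make the sentence correct.

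A reader might infer that the before-after analyses as a whole use unsuitable tests. The document does not support that: the dependent t test and the GEE fit the data. Nor does it say how BDNF is distributed, so whether the fallback will be used for BDNF is unknown.

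The power figures are also open to challenge. They use normal data, which under this plan would normally go to the t test, and they depend on correlations that the article does not give. They show the direction and possible size of the effect and do not forecast this study's loss. At the positive correlations examined the error is conservative, so it costs power and does not inflate false positives.

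A reader might also infer that continuous outcomes will be dichotomised for logistic regression. That is not established. The word appears once, in the abstract, no split is described anywhere, and an article may leave the regression type to a fuller document. What remains is a discrepancy between two statements in the same article.

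**Conclusion.** The rank-test sentence is wrong as written and should be corrected. Its effect is confined to related comparisons of outcomes that fail the normality check. This could include BDNF change, the comparison behind the 42 per group. In the illustration, power ranges from about 79% (no loss) at an assumed correlation of 0 to about 23% at 0.7, against about 78% for the signed-rank test. These figures assume 32 pairs, normal data and the planning difference and SD. The stated sample size does not change.

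The confounder point is secondary. It is an inconsistency to reconcile, and the document does not show that a wrong analysis has been chosen.

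**What to change.** In Statistical Analysis, replace the rank-test wording with: *Wilcoxon signed-rank test for related samples and Mann–Whitney U test for unrelated samples.*

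For confounders, state one method in both the abstract and Statistical Analysis. Any of these would resolve the discrepancy:

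- linear regression on the continuous score;
- covariate adjustment within the GEE;
- logistic regression, if that is what is meant, with the binary outcome and its cut-off defined.

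Under either of the first two, enter number of sessions and medication use as measured at follow-up, not as baseline-only covariates, in line with Table 1.

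The cost is a few words in two places. No data collection, outcome or sample size changes.

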#### Confusion/Mediator/Moderator Factors

The mediating factors will be therapeutic alliance, motivation, and defense mechanisms (for PDT only). The moderating factors will be gender, age, religiosity, stressors, social support, personality traits, and defense mechanisms (for CBT and IPT). The confounding factors considered will be diagnosis, medication use, number of sessions, and comorbidities.

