## Discussion

The only naturalistic longitudinal study that we found concluded that there was no significant difference in outcomes between therapies, as well as among therapists. However, these results need to be viewed with caution given some limitations related to loss, incomplete data, and the lack of long-term follow-up. Our study used direct contact with patients, which increased the number of variables and collection of BDNF as a possible biomarker in response to psychotherapy intervention.

Historically, studies in psychotherapy have been difficult to perform because they involve multiple factors and variables that are interrelated. Many variables may act as only associated factors, and others (e.g., mediators, predictors and even as confounders) may have varying effect sizes. We had difficulty defining some variables as mediators or confounders because the mechanism by which psychotherapies work is a matter of debate (54). We are interested in determining what is common to all psychotherapies. Therefore, we relied on published studies (16) and clinical experience.

Regarding the biological factors, studies of biomarkers such as BDNF may provide insights into the possible mechanisms of illness and recovery from serious disorders such as depression, bipolar disorder, and schizophrenia (22). A few studies have evaluated this neutrotrophin in the context of psychotherapies (29, 55). However, the mechanisms by which long-term psychotherapies produce changes in neuronal circuits and biomarkers, such as BDNF, have not yet been determined. In addition, most existing studies are characterized by follow-up durations of fewer than 12 weeks. As a result, they may be unable to detect changes that occur more slowly than those observed in BDNF with psychotropic drugs (56).

Considering the severity profile of patients referred to a tertiary medical center and the level of experience of resident physicians, the magnitude of improvement is lower than in other more favorable clinical settings. This improvement should be more pronounced in the 12-month follow-up considering the long-term effects of psychotherapies. The level of therapeutic alliance may possibly mediate this improvement. We believe that it will also reflect patients’ psychosocial factors and increase BDNF.

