Limitations of this study include the heterogeneity of the training and experience of the resident psychiatrists and the absence of evaluation from their point of view in the psychotherapeutic process. As a study is naturalistic, there is no way to control the impact of the researchers’ interviews. We will collect a series of demographic data, use of medications, and number of sessions to control possible confounders, but we know that because it is an open study, there is no way to control all differences between groups. Also, psychotherapy studies often have large amounts of losses (16). To control this bias, we will compare the clinical and demographic characteristics of the lost sample with those that continue in relation to the baseline. As for the multiplicity of diagnoses that may be found, to homogenize the sample, we will consider for inclusion the BDI value >15.

Studies such as this one seek to contribute to the foundations of public health policies and investments for the treatment of patients with severe mental illnesses who are at risk of hospitalization and suicide. These types of investigations also seek to promote mental health, rehabilitation, and social reintegration. Understanding the mediating and biological mechanisms of the psychotherapeutic process can help to optimize these interventions and facilitate their indication according to the psychopathological profile and the severity of the patients.

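### The article does not say that its mediation models carry the confounders, and no confounder list names baseline symptom severity, so the mediator-outcome path can be spurious

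*Protocol article*

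**What the plan says.** The Statistical Analysis section assigns one method to each task: "The Hayes method will be used to analyze the mediators (52), and the multivariate regression will be used to analyze the confounders". The Abstract makes the same division and calls the second model logistic: "the analysis of mediators by the Hayes method, and confounders by multivariate logistic regression". Neither place names covariates for the mediation models.

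Mediation is a secondary hypothesis. The Aims expect that "the mechanisms of improvement will be mediated by the therapeutic alliance, motivational status, and defense mechanisms (for PDT"), and the section on confusion, mediator and moderator factors repeats the three mediators. The Discussion adds, cautiously: "The level of therapeutic alliance may possibly mediate this improvement".

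Confounders are listed in three places:
- Aims: "The confounders of this therapeutic improvement will be number of sessions, comorbidities, and medication use".
- Confusion/Mediator/Moderator Factors: "The confounding factors considered will be diagnosis, medication use, number of sessions, and comorbidities".
- Limitations paragraph of the Discussion: "We will collect a series of demographic data, use of medications, and number of sessions to control possible confounders". No model is named there.

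Baseline symptom severity appears in none of them. Table 1 schedules the BDI, BAI and SCL-90-R at baseline, 6 and 12 months, and alliance (CALPAS) and motivation (URICA) at the same three visits. Under Participants, modality is chosen by clinical judgment. Under Design, the baseline window stays open until the fourth session.

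**The concern.** A confounder corrects an indirect effect only if it sits inside the mediator and outcome equations. Estimating it in another regression leaves the indirect effect unchanged. Severity is an obvious candidate here: less ill patients may form a better alliance, be more motivated and also finish with fewer symptoms. The entry criterion of BDI above 15 sets a floor, and severity still varies above it.

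Even a reader who places every listed confounder in the Hayes model would leave severity out, because no list contains it. At stake is the secondary hypothesis that alliance and motivation carry the improvement: an association due to severity could be reported as a mechanism. The primary analyses are not affected.

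**Working it through.** **Plan's own figures.** The article gives no figure for the mediation analysis. Its 42 per group is sized on BDNF before and after therapy. It is approximately reproduced by a paired test: ((1.960 + 0.842) × 0.43 / 0.22)² = 29.98, so 30, which becomes 38, 40 or 43 after losses of 20%, 25% or 30%. That figure is not in dispute here.

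**Inputs from the article.** 126 patients; 42 per modality; losses of 20-30%; two-sided 5%. Completers: 126 × 0.70 = 88 and 126 × 0.80 = 101 overall; 42 × 0.70 = 29 and 42 × 0.80 = 33 (rounded down) per modality.

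**Assumptions.** True mediator effect zero; severity-mediator correlation 0.1 to 0.4 in absolute value; severity-outcome correlation 0.4 to 0.6.

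**Step 1: mediator-outcome path, all completers, severity omitted.** The spurious correlation is the product r = r(severity, mediator) × r(severity, outcome). By Fisher's z, the chance of false significance is approximately Φ(atanh|r| × √(n − 3) − 1.960), plus a small opposite tail. Example: 0.4 × 0.6 = 0.24; atanh 0.24 = 0.2448; at n = 101, 0.2448 × √98 = 2.423; Φ(0.463) = 0.68.

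| Severity-mediator \|r\| | Spurious \|r\| | Falsely significant, n = 88 to 101 |
|---|---|---|
| 0.1 | 0.04-0.06 | 7-9% |
| 0.2 | 0.08-0.12 | 12-22% |
| 0.3 | 0.12-0.18 | 20-44% |
| 0.4 | 0.16-0.24 | 32-68% |

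**Step 2: full indirect effect, two modalities.** Simulation with 29 or 33 per arm, 2,000 runs per cell, ordinary least squares for both paths, and mediation declared when both are significant. The two-modality contrast is an assumption. Severity-mediator and severity-outcome correlations were −0.2/0.5, −0.3/0.5 and −0.4/0.6.

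Without severity in the model, the mediator-outcome path alone was falsely significant in 11-14%, 20-25% and 42-51% of runs for those three pairs. The false indirect effect was:

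| Modality-mediator association | Unadjusted |
|---|---|
| None | 1-3% |
| Only through a severity difference of 0.5-0.8 SD between modalities | 1-11% |
| Modality truly shifts the mediator by 0.5-0.8 SD | 6-43% |

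With baseline severity in both equations, the path was significant in 4-6% of runs with a mean coefficient near zero, and the false indirect effect was at most about 5% in every cell.

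**Step 3: direction.** For final symptom scores, severity makes higher alliance go with fewer symptoms. For change scores (final minus baseline, equal SDs assumed), baseline correlates with change at −√((1 − r)/2), where r is the baseline-final correlation: −0.50 at r = 0.5 and −0.45 at r = 0.6. With severity-alliance correlations of −0.2 to −0.4, the spurious alliance-change correlation runs from 0.2 × 0.45 = +0.09 to 0.4 × 0.50 = +0.20, so higher alliance goes with less improvement. The article does not say which score is used.

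**The case against.** The strongest reply is that the text is silent rather than wrong. No sentence says that the Hayes models run without covariates, the method is regression-based and accepts them, and a condensed article may leave a covariate list to the full protocol or SAP. The Discussion also declares an intent to control confounding, and concedes that not all group differences can be controlled. This stands against reading the article as saying that the paths are unadjusted; a reader might infer that, but it is an inference. It does not answer the stated split between methods, or confounder lists that are explicit and leave severity out.

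A reader might also infer that severity alone makes alliance look like a mediator, or that a false finding is to be expected. Neither is supported. The 7-68% concerns one path and is not a false-mediation rate: without a modality-mediator association, false mediation is 1-3%. Only the cells at a severity-mediator correlation of 0.4 reach one half, and at 0.1 the inflation is slight. Nor does the bias necessarily favour the hypothesis, since its sign depends on the outcome score.

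Two objections to over-adjusting also stand. Baseline alliance may be measured as late as session four, so forcing it into the model can remove early alliance that belongs to the hypothesised mechanism. Number of sessions is a listed confounder but arises after baseline.

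**Conclusion.** The concern holds in a limited form. The article separates the mediator and confounder analyses, does not state that the mediation models carry the confounders, and omits baseline severity from every list while collecting it. In a non-randomised design, a model run as described is open to a spurious mediator-outcome path, falsely significant in about 7-68% of studies under the assumed correlations. For the full indirect effect the false rate is 1-11% unless modality truly shifts the mediator, when it is 6-43%. All of these rates depend on correlations that the documents do not give. The point is worth correcting because the remedy uses data already scheduled, but it concerns a secondary hypothesis only.

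**What to change.** - Add baseline symptom severity to the confounder list.
- State that both equations of each Hayes model include the baseline value of the outcome and the pre-treatment confounders: diagnosis, comorbidities and baseline medication.
- State whether the outcome is a final score or a change score.
- Report the adjusted indirect effect with its bootstrap interval, and describe it as associational.
- Adjust for the baseline mediator in a sensitivity analysis, because the baseline window runs to session four.
- Do not enter number of sessions as if it were a baseline covariate; if it is used, justify it separately.

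The cost is a sentence or two and a few degrees of freedom. Diagnosis and comorbidities may need several terms, which will be felt most in the PDT-only defense-mechanism model with about 29-33 completers. Indirect effects will probably be smaller. No new data are needed.
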